### Data Collection Procedure

#### Pilot Study

After receiving information about the project in the form of a video and giving informed consent, the mentees will receive an individual link to participate in a Web survey. Questions on the mentee survey at program commencement will focus on social capital in the form of relationships with friends, native Norwegians, connectedness to the school environment, and to Norway more broadly. This will be used to test out and adjust measures for the full RCT study based on feedback from the groups. A Web survey will be administered at program completion, with the same survey questions as on the first survey, supplemented with questions about program fidelity (outputs) and a short battery to assess the relationship with the mentor and implementation. Mentors will receive surveys related to program fidelity and the relationship with mentees and staff. Additionally, both mentees and mentors will respond to survey questions on the usability of the digital platform. To supplement the quantitative survey data, qualitative data will be collected from mentors and mentees in interview form for both the pilot and RCT. Individuals will be selected for interviews based on characteristics such as age, sex, immigration background, and length of time in Norway, with a goal to get a very diverse group [38]. Interview questions will address barriers and facilitators to implementation, possible contextual factors relevant to the implementation and participants’ experiences of these factors, and the acceptability and meaningfulness of the measures used in the survey (see Outputs in the Measures section for details on the operationalization of these concepts). Questions to program staff will focus on resources such as program staffing, finances, and technical support for the digital platform.

The pilot study has been approved by the Data Protection Office at Oslo University Hospital. All pilot study data will be stored on a secure remote server as per Oslo University Hospital Personal Data Protection regulations. The pilot study is funded by a grant from the Norwegian Research Council and is a partnership between the Center for Shared Decision Making and Collaborative Care Research at Oslo University Hospital, NORCE-Norwegian Research Centre, Halmstad University, the Norwegian Labor and Welfare Administration (NAV), and Fretex.

#### Full Study With Randomized Controlled Trial

The effects of the program as a social capital intervention will be studied using a two-level clustered randomized trial, with schools randomly assigned as intervention or control schools. The analyses will be at the individual level. In using a randomized comparison of mentees with non-mentees, the effects of mentoring on social capital can be assessed, also controlling for individual differences.

Youth in both the intervention and control groups will complete Web surveys. The youth surveys cover questions related to social capital and will be conducted at baseline (before program commencement), six months after the baseline measurement (at program completion for the intervention groups), and six months after program completion (12 months after the baseline measurement). Surveys to youth in the control group will be administered at the same time points as for the mentees. Mentors will respond to surveys at program conclusion. Because youth in the intervention group will receive mentoring outside of the school environment, we do not have a specific activity planned for the control group. However, control group youth will be put on a waiting list to participate in the mentoring program after study completion, if they desire. Approval from the institutional ethics board (Data Protection Officer) will be applied for and obtained before RCT study commencement.

The following table (Table 1) summarizes the instruments, respondents, and timeline for data collection.

**Table 1 table1:** Overview of the study procedure.

Study stage and data collection instrument		Respondents	Description	Time point

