Although approaches for strengthening social capital are clearly worth pursuing, interventions to increase youth social capital, such as the one proposed in this paper, are quite new [23]. Little is known about how such interventions might be implemented, and their effects [24]. Although not systematically studied as such, mentoring programs have the potential to act as “social capital interventions” by assisting immigrants in expanding their networks, and thus their social capital [25,26]. In this setting, mentoring can be defined as “taking place between young persons (ie, mentees) and older or more experienced volunteers (ie, mentors) who are acting in a nonprofessional helping capacity to provide relationship-based support that benefits one or more areas of the mentee’s development” [27]. Participation in youth mentoring programs is associated with improved outcomes across social, behavioral, and academic domains [28]. Such programs, typically conducted by social entrepreneurs, have few traditions in Norway. For the program described in this paper, coordinators recruit, select, train, and match mentors and mentees, and all mentees receive the same basic program. Main program components include training for both mentors and mentees before program start, mentee and mentor sharing of their achievement story (a proud life moment), identification and discussion of mentee strengths, a “roadmap” selecting a goal and describing tasks for the mentee to achieve it, and a network mapping exercise for the mentees. Additionally, the program requires six face-to-face dyad meetings, with one meeting each month during the six-month program period. Staff members also follow up on the matches monthly. Mentees are recently arrived immigrant youth recruited from local schools; willingness and interest in participating are the main selection criteria. Mentor volunteers are recruited in a variety of ways, including personal connections with program staff, social media, and volunteer recruitment websites.

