**Randomized controlled trial**				
	Web survey at program start (baseline)	Mentees; control group youth	Pre-post social capital measurements; demographic variables	Program start (estimated fall 2020)
	Web survey at program completion	Mentees; mentors; control group youth	Pre-post social capital measurements; program fidelity	Program completion (6 months after program start)
	Postprogram survey after program completion	Mentees; control group youth	Pre-post social capital measurements	Follow-up 6 months after program completion (12 months after program start)
	Interviews	Mentees (10-20); mentors (5-10); program staff (4)	Supplementary information on social capital based on survey responses	Midway and at the end of the program (fall and winter 2020)

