#### Outputs: Intervention Implementation

Outputs are the process and mechanisms by which the “problem” and its consequences are targeted. More specifically, this is the implementation of the intervention. An important emphasis is on fidelity of implementation of core program components (including dose, or the amount of the intervention, and reach), and mechanisms of impact (participants’ interactions with the intervention) and the contextual factors that have an impact on the implementation (discussed subsequently). Assessment of fidelity is done using a self-developed scale for the study to match the program environment. Program fidelity is measured using the following indicators (previously described under Background and Context): the total number of dyad meetings held with at least one dyad meeting each month (six meetings in all), participation in training before program start, and execution of the main program components, such as network mapping. The proportion of participants that complete the program (reach) will also be assessed. Identification of any deviations or adaptations to these key program components will be noted. Because the intervention also includes a digital component (forums for mentor-mentee contact), log data from the platform, including the number of log-ins and time spent on different parts of the platform, will be analyzed to assess dosage.

Relationship quality (mechanism of impact) will be measured using the 14-item Mentor Strength of Relationship scale [40], adapted from the Big Brothers Big Sisters mentoring context to this context (eg, terminology such as “my Little” is replaced with “my mentee”). Answers are scored on a five-point Likert scale (“strongly disagree” to “strongly agree”). For mentees, the positive statements from the Youth Strength of Relationship Scale [40,41] will be used; response categories are on a five-point scale and range from “not true at all” to “always true.” The Strength of Relationship scales have been assessed for fit using confirmatory factor analysis, with acceptable results [40]. Little research has been conducted on mentee or mentor relationships with program staff and program training. Therefore, self-developed single items will be used that ask to what extent respondents were satisfied with the program coordinator and the training they received (response categories from 1=“very dissatisfied” to 5=“very satisfied”).

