## Discussion

The overall objective of this protocol was to present a plan for evaluating the implementation and effects of digitally augmented mentoring relative to social capital among immigrant youth. The main working hypothesis is that students who receive the intervention will have broader networks and higher levels of trust and feelings of belonging (greater social capital) compared with those students who do not receive the intervention. Considering the paucity of research on social capital interventions, the protocol should be relevant for researchers interested in community-based health promotion and in social capital more broadly. More specifically, it provides a framework for analyzing mentoring programs for immigrant youth to see what works under what circumstances and for whom. However, there are some anticipated limitations.

Because mentees self-select to the program in the pilot study, these findings may not be generalizable to a larger group; however, this is not the primary objective of the pilot. The RCT should ameliorate this issue owing to the random selection of individuals and classes. Another potential limitation relates to language issues, particularly in the survey instrument. The pilot study is intended to assess the relevance and acceptability of the instruments to the target groups; comprehension will also be a relevant consideration at this stage. Thus, this issue will hopefully be minimal in the RCT. Attrition, particularly after program completion, is another potential limitation, as in most survey research.

If this intervention is successful, it may have an impact on the possibility for young people to be better included in Norwegian society. Further work could potentially encompass cost-benefit analyses if there is support for the hypotheses. These preliminary results from the pilot and RCT, if positive, could be promising for a potential expansion of the intervention to other contexts and target groups.

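### The contrast called randomised is mentees against non-mentees, but only schools are randomised and mentoring is entered by interest, so self-selection can re-enter between the arms

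*Protocol article*

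**What the plan says.** All references are to the protocol article.

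- **Unit randomised.** Full Study With Randomized Controlled Trial describes a "two-level clustered randomized trial, with schools randomly assigned as intervention or control schools". Sample and Participant Recruitment adds a random draw of classes within the schools of each arm. Neither section selects or assigns individuals at random.
- **Contrast.** The Full Study section continues: "In using a randomized comparison of mentees with non-mentees, the effects of mentoring on social capital can be assessed". It also says: "The analyses will be at the individual level". Adjustment for differences between individuals is mentioned.
- **Entry to mentoring.** Background and Context says of mentees that "willingness and interest in participating are the main selection criteria". This describes the programme in general. Further RCT eligibility criteria are to follow from the pilot.
- **Who is surveyed.** For the baseline and 12-month RCT surveys, Table 1 gives the respondents as "Mentees; control group youth"; the 6-month row adds mentors. No row covers youth in intervention classes who do not become mentees.
- **Control youth.** No activity is planned for them, and "control group youth will be put on a waiting list to participate in the mentoring program after study completion, if they desire". No interest in mentoring is stated as a condition of entry.
- **Self-selection.** The Discussion grants that pilot mentees select themselves, which limits generalisability, and then says: "The RCT should ameliorate this issue owing to the random selection of individuals and classes".

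**The concern.** Randomising schools makes one comparison fair: all youth enrolled under the same rule in intervention schools against all youth enrolled under that rule in control schools. It does not make it fair to compare the subset of one arm that wanted mentoring with control youth who were never asked.

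Willingness to take part plausibly goes with trust, belonging and social contact, which are the outcomes themselves. If it filters one arm only, some of the observed difference may reflect who came forward and not what mentoring did. Age, sex and time in Norway, which the article lists among its controls, do not measure willingness.

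This cannot be left to the analysis plan. If youth who decline mentoring in intervention schools are never enrolled or surveyed, no later analysis can bring them back.

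**Working it through.** The article gives no sample size, effect size, SD or intracluster correlation for the RCT, so there is no stated figure to reproduce. The check has two parts.

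**1. The sections side by side**

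- Random assignment applies to schools and random drawing to classes. Individuals are neither assigned nor selected at random anywhere in the Methods.
- The named contrast is nevertheless between individuals who are mentored and individuals who are not.
- If mentoring is voluntary, some youth in drawn intervention classes may decline. Table 1 gives them no respondent category. Sample and Participant Recruitment also keeps participants and non-participants in separate schools, which under voluntary uptake fits only if decliners are outside the study.
- Control youth may take up mentoring later if they wish, so some may not want it. Nothing filters them on the same trait.
- The individual-level random selection credited in the Discussion therefore has no counterpart in the design.

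**2. How large the effect could be (illustration)**

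Assumptions, none of them from the document: a true mentoring effect of zero; a share p of control youth who would have volunteered; willing youth scoring g SD higher than unwilling youth.

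- Mean of mentees (all willing) relative to unwilling youth: g.
- Mean of control youth on the same scale: p × g.
- Spurious difference, post-only: g − p × g = (1 − p) × g.

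False-positive rate of a two-sided 5% z-test with b = (1 − p) × g and SE = √(2/n), ignoring clustering and adjustment: 1 − Φ(1.96 − b/SE) + Φ(−1.96 − b/SE). The article expects several hundred youth in two halves; n = 100 and 200 per arm are assumed.

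| p | g | (1 − p) × g | n = 100 | n = 200 |
|---|---|---|---|---|
| 0.3 | 0.5 | 0.7 × 0.5 = 0.35 SD | 69.7% | 93.8% |
| 0.5 | 0.3 | 0.5 × 0.3 = 0.15 SD | 18.6% | 32.3% |
| 0.7 | 0.2 | 0.3 × 0.2 = 0.06 SD | 7.1% | 9.2% |
| 0.9 | 0.2 | 0.1 × 0.2 = 0.02 SD | 5.2% | 5.5% |
| 1.0 | any | 0 | 5.0% | 5.0% |

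The bias does not shrink with n, so a larger trial raises the false-positive rate. Allowing for clustering would widen the SE and lower these rates.

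**What baseline data do to this.** If the gap g is the same at baseline and follow-up, the difference in change is (1 − p)g − (1 − p)g = 0. If willing youth change by h SD more than unwilling youth for reasons other than mentoring, (1 − p) × h remains. The document gives no information on h, and its sign could go either way.

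**The case against.** The strongest reply is that mentees is shorthand for the intervention arm. The sentence about mentees and non-mentees follows directly on random assignment of schools, the same section speaks of surveying both groups, and participants are kept out of control schools. The willingness criterion describes the general programme, RCT eligibility is still open, and consent is voluntary for youth in both arms. Moreover, social capital is measured at baseline in both arms and pre-post measures are planned, so the post-only figures overstate what would remain.

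Much of this stands. Unequal screening is possible under the text, not fixed by it, and the figures are an upper illustration. But the shorthand is carried into the respondent list, and the article nowhere says that interest is established equally in both arms. Baseline data remove a constant gap, not a difference in how willing youth change.

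Stronger readings that a reader might infer are not supported:

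- **That the protocol claims the RCT eliminates self-selection.** It claims only improvement, and on generalisability, not on confounding between arms.
- **That baseline falls after mentee training.** The Full Study section places baseline ahead of the programme, Table 1 places it at programme start, and the fidelity indicators include "participation in training before program start". The order of survey and training is not stated.
- **That youth who stop mentoring leave the surveys.** Nothing says so.
- **That the lack of an intention-to-treat statement is itself a fault.** Such a statement commonly sits in the full protocol or analysis plan, which are not shown.

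**Conclusion.** The point holds in limited form. The text calls a participation-based comparison randomised when only schools are randomised, and its entry criterion and respondent list let self-selection re-enter between the arms. The Discussion's appeal to randomly selected individuals has no basis in the Methods.

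The document does not show that bias will occur, how large it would be, or which way it would run. Under the assumed p and g a post-only comparison could be off by 0.06 to 0.35 SD, and by almost nothing if nearly all control youth would volunteer. Baseline adjustment or change scores would lessen it without guaranteeing its removal. A reader might conclude that the result must favour mentoring; that does not follow, since motivated youth who start higher on bounded scales could also gain less.

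It matters because it concerns the trial's main contrast and cannot be repaired after enrolment.

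**What to change.** 1. Apply one enrolment rule to both arms. Before a school's allocation is disclosed, obtain study consent and record whether each youth wants mentoring, either now or after the waiting period.
2. Take the baseline survey before that disclosure and before any mentee training, and state this order.
3. In the Full Study section and Table 1, replace the mentee and non-mentee labels with all enrolled youth in intervention schools and all enrolled youth in control schools. Follow them at 6 and 12 months whether or not they start or finish mentoring, and compare them by assigned school.
4. In the Discussion, delete the reference to randomly selected individuals or bring it into line with the Methods, and make Background and Context consistent with the RCT entry rule.

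With interest defined alike in both arms, the selection term is zero (the p = 1.0 row) under the same assumptions. The costs are an earlier consent and baseline step and a few more youths to survey. The results would apply to youth interested in mentoring, and non-starters would dilute the estimate. The Results section says RCT recruitment starts only after the pilot, so there is time to make the change.

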**Pilot**				
	Web survey at program start (baseline)	Mentees (approximately 40)	Social capital: cognitive and structural); demographic variables	Program start (fall 2019)
	Web survey in program middle and conclusion	Mentees (approximately 40); mentors (approximately 40)	Usability of digital platform	Mid and end of program
	Web survey at program completion	Mentees (approximately 40); mentors (approximately 40)	Same as baseline survey; program fidelity	Program completion (6 months after start; spring 2020)
	Interviews	Mentees (5-10); mentors (5); program staff (2)	Acceptability and relevance of social capital measures; barriers and facilitators to implementation and fidelity	Midway and at the end of the program (fall 2019, spring 2020)
**Randomized controlled trial**				
	Web survey at program start (baseline)	Mentees; control group youth	Pre-post social capital measurements; demographic variables	Program start (estimated fall 2020)
	Web survey at program completion	Mentees; mentors; control group youth	Pre-post social capital measurements; program fidelity	Program completion (6 months after program start)
	Postprogram survey after program completion	Mentees; control group youth	Pre-post social capital measurements	Follow-up 6 months after program completion (12 months after program start)
	Interviews	Mentees (10-20); mentors (5-10); program staff (4)	Supplementary information on social capital based on survey responses	Midway and at the end of the program (fall and winter 2020)
**Pilot and randomized controlled trial**				
	Qualitative and metadata from the digital platform	Mentees; mentors	App use data (frequency, length of time, particular modules used); content of forum posts	Throughout the programs

### Measures

Measures to be used for the study survey are adapted from previous research and large-scale cross-national surveys [40-48]. Where relevant, new items were developed specifically for this intervention context, particularly to measure fidelity of implementation.

#### Outputs: Intervention Implementation

Outputs are the process and mechanisms by which the “problem” and its consequences are targeted. More specifically, this is the implementation of the intervention. An important emphasis is on fidelity of implementation of core program components (including dose, or the amount of the intervention, and reach), and mechanisms of impact (participants’ interactions with the intervention) and the contextual factors that have an impact on the implementation (discussed subsequently). Assessment of fidelity is done using a self-developed scale for the study to match the program environment. Program fidelity is measured using the following indicators (previously described under Background and Context): the total number of dyad meetings held with at least one dyad meeting each month (six meetings in all), participation in training before program start, and execution of the main program components, such as network mapping. The proportion of participants that complete the program (reach) will also be assessed. Identification of any deviations or adaptations to these key program components will be noted. Because the intervention also includes a digital component (forums for mentor-mentee contact), log data from the platform, including the number of log-ins and time spent on different parts of the platform, will be analyzed to assess dosage.

Relationship quality (mechanism of impact) will be measured using the 14-item Mentor Strength of Relationship scale [40], adapted from the Big Brothers Big Sisters mentoring context to this context (eg, terminology such as “my Little” is replaced with “my mentee”). Answers are scored on a five-point Likert scale (“strongly disagree” to “strongly agree”). For mentees, the positive statements from the Youth Strength of Relationship Scale [40,41] will be used; response categories are on a five-point scale and range from “not true at all” to “always true.” The Strength of Relationship scales have been assessed for fit using confirmatory factor analysis, with acceptable results [40]. Little research has been conducted on mentee or mentor relationships with program staff and program training. Therefore, self-developed single items will be used that ask to what extent respondents were satisfied with the program coordinator and the training they received (response categories from 1=“very dissatisfied” to 5=“very satisfied”).

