### Objectives and Significance

This paper describes a protocol for studying a digitally augmented mentoring program as a social capital intervention for immigrant youth in Norway. The protocol proposes a pilot study followed by a randomized controlled trial (RCT). Ultimately, we are interested in assessing the implementation and effects of mentoring program participation on social capital. A process evaluation framework inspired by a previous study [32] will be applied for investigating the implementation of the mentoring program in this pilot study. This framework consists of (1) contextual factors that affect the implementation, (2) what has been implemented and how, and (3) mechanism of impact (ie, the participants’ responses to and interactions with the program). Thus, the objective of the pilot study is to assess program fidelity and design by investigating the context, implementation process, and mechanisms of impact [32,33]. The questions guiding the pilot study are:

What contextual factors affect the implementation?How is the mentoring program implemented (ie, fidelity, dose, and reach)?What are the participants’ experiences in the mentoring program?Are the measures used for studying outputs and outcomes valid, and are they acceptable and meaningful to stakeholders?

The pilot allows adjustments of the social capital intervention before full-scale implementation and the RCT. The intention of the RCT is to investigate the effects of the implemented program on the social capital of immigrant youth, guided by the following questions:

To what extent was the intervention implemented (outputs)?What are the effects of the implemented program on social capital indicators (outcomes)?What is the relationship between program fidelity and effects?

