## Methods

### Study Design

The first stage is the pilot study, followed by the RCT. A mixed-methods approach will be used combining quantitative survey instruments (pre-post test design) with qualitative data from interviews and focus groups [38]. The survey will measure outputs (program fidelity, dose, and reach); outcomes (cognitive and structural social capital), which are a result of the implementation outputs; and contextual factors (respondents’ demographics, school characteristics, and usability of the digital platform). Specific cutoffs for assessing fidelity to the core program components (described in the Background and Context section) and effectiveness will be developed based on pilot study results. Interviews with mentors, youth, and program staff will allow a detailed qualitative understanding of the mechanisms occurring and stakeholder experiences.

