### Sample and Participant Recruitment

Both stages of the study will be conducted in close cooperation with mentor program staff (the individuals working directly to coordinate, match, train, and follow up on dyads), and with feedback from the youth. The primary unit of analysis for the study is recently arrived immigrant youth, ages 15 to 25 years, attending school. These youth will be in or have completed their first year of Norwegian schooling; therefore, they will have a minimum basic level of Norwegian proficiency. We will offer interviews in Norwegian and English, but will also consider the use of a translator, as necessary, for the RCT to gain a better understanding of the experiences of participants with varying levels of Norwegian language comprehension. Information from mentors and program staff will also be collected. Informed consent will be obtained and the voluntary nature of participation will be emphasized to the youth, with information that they can end their participation at any time. A video will be used to present the research project, handling of data (confidential, but not anonymous), and privacy issues in youth-friendly language to gain fully informed consent and to increase stakeholder (youth) involvement and interest [39].

For the pilot study, all mentees (approximately 40) participating in four of the mentoring programs will be recruited to participate in the survey at the beginning and end of the program. The majority of these mentees have backgrounds from Syria and Eritrea, and almost all will be attending school. At the end of the six-month program, mentors (approximately 40) from these programs will also be invited to respond to a survey. All mentee respondents will receive small denomination gift cards (approximately $28) on completion of the surveys as a gesture of appreciation for their assistance with the project. We will also discuss how the youth perceive receiving gift cards, with a specific focus on any feelings of coerciveness, to make any adjustments before the RCT. Qualitative respondents will be selected from the individuals providing quantitative information to investigate specific aspects of program fidelity and implementation in more detail.

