The full-scale RCT will recruit participants from Norwegian schools and include both a control and an intervention group. The study will try to select similar schools for both groups regarding school size, socioeconomic characteristics, and school type (age range of the student body). Within the intervention group of schools, intervention classes will be drawn randomly, whereas control classes will be drawn randomly from the control schools. Participants and nonparticipants will not attend the same schools to avoid contagion effects. The exact number of individuals will be estimated based on a power analysis of data from the pilot study and is anticipated to encompass several hundred youth. Half will be in the intervention group and half in the control group. Students who are not assigned to the control groups for the study will have the opportunity to receive the intervention after the study has concluded. Although all the youth will have a basic level of Norwegian proficiency, additional potential inclusion and exclusion criteria for the RCT will be developed based on findings from the pilot study. Similar to the pilot study, mentors will be surveyed at program conclusion, and respondents will be invited to qualitative interviews and focus groups, to supplement and nuance the quantitative data.

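### Reach is defined as completion among participants, so the reach figure cannot show low uptake of a voluntary program

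*Protocol article*

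**What the plan says.** Reach is one of the implementation quantities the study sets out to measure. In Objectives and Significance, a pilot question asks "How is the mentoring program implemented (ie, fidelity, dose, and reach"). Study Design repeats the list: "The survey will measure outputs (program fidelity, dose, and reach"). In both places reach stands beside fidelity and dose as an item of its own.

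The only working definition is in Outputs: Intervention Implementation: "The proportion of participants that complete the program (reach) will also be assessed". No other section gives a different denominator, and none describes counting youth who were eligible, invited or declined.

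Three further statements bear on who the participants are:

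- In Background and Context, on how mentees enter the program: "willingness and interest in participating are the main selection criteria".
- In Sample and Participant Recruitment, for the pilot: "all mentees (approximately 40) participating in four of the mentoring programs will be recruited to participate in the survey".
- In the same section, for the RCT: "Within the intervention group of schools, intervention classes will be drawn randomly".

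The Discussion concedes self-selection, for the pilot only: "Because mentees self-select to the program in the pilot study, these findings may not be generalizable to a larger group". It expects the RCT to lessen the problem because people and classes are selected at random.

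**The concern.** A ratio with participants in the denominator describes what happens after youth have joined. It does not describe how far the program got into the group it was meant for. When joining is voluntary these can differ widely: a program that few take up but nearly all finish would be reported as having high reach.

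Two uses of the figure are at stake. First, Analytical Framework says the pilot allows adjustments before the RCT when certain outputs fall short. A reach figure that does not move with uptake cannot prompt an adjustment for poor uptake. Second, drawing classes at random does not make joining compulsory for the youth in them. Uptake within the drawn classes is what would let a reader judge whether the RCT results speak for those classes, and the stated measure leaves it out.

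**Working it through.** The article states no value for reach, so there is no figure to reproduce. The check is of the definition.

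**Quantities.** E = eligible (or invited) youth, S = youth who start, C = youth who complete.

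- Stated reach, taking participants as starters: C / S
- Uptake: S / E
- Completion among the eligible: C / E = (S / E) × (C / S)

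E does not appear in C / S, so the stated measure cannot respond to uptake.

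**RCT illustration.** The article gives no eligible count, uptake or completion rate. Assume E = 100 and C / S = 0.90.

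| Starters S | Completers C = 0.90 × S | Stated reach C / S | Uptake S / E | Completion among eligible C / E |
|---|---|---|---|---|
| 20 | 18 | 90% | 20% | 18% |
| 50 | 45 | 90% | 50% | 45% |
| 80 | 72 | 90% | 80% | 72% |

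The last two columns are different measures. Reach in the sense proposed here is the uptake column.

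**Pilot illustration.** The article gives about 40 mentees, already enrolled. Assume 36 complete, so stated reach is 36 / 40 = 90%. If 40, 80, 200 or 400 youth had been invited (assumed), uptake would be 40/40 = 100%, 40/80 = 50%, 40/200 = 20% or 40/400 = 10%. Stated reach stays at 90% throughout.

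**Alternative reading for the RCT.** Suppose *participants* means all youth allocated to the intervention, whether or not they start.

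- If all 100 eligible youth consent and are counted, the measure becomes C / E: 18%, 45% or 72%. It then responds to non-starting, but combines uptake and completion in one number.
- If those who do not want mentoring decline at consent, so that consenters and starters are the same youth, it returns to 18/20, 45/50 or 72/80, which is 90% each time.

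Under either reading, non-consenting eligible youth are not counted.

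**The case against.** The strongest objection is that nothing is hidden. Numerator and denominator stand in one sentence, so a reader can see that the measure is a completion proportion. No section promises coverage of the eligible population, and the same section treats reach as part of fidelity. That much is fair, and overlap with the fidelity indicators is not itself an error. But the article also lists reach separately from fidelity and dose, and nothing else in it records who was offered the program and did not join. The choice therefore leaves a gap as well as a loose label.

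A second objection is that *participants* is ambiguous in the RCT. Sample and Participant Recruitment contrasts participants with nonparticipants by school, which could make every allocated youth a participant. This stands in part: it would bring in consenting youth who never start, but not those who refuse consent.

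A third is that recruitment-flow counts are often left to a fuller protocol. That would excuse silence about the counts. Here, however, a definition is stated, and it would have to be changed for such counts to enter it.

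A reader might also infer stronger points that the article does not support:

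- *That the trial's effect estimate is biased.* Reach is an implementation output and does not enter the comparison of social capital between arms.
- *That the implementation questions cannot be answered.* Meeting counts, training, execution of components, noted deviations and platform logs still inform them, and the RCT question on outputs does not name reach.
- *That RCT mentees will be a small self-selected part of their classes.* The statement about willingness describes the program in general, the conceded self-selection is the pilot's, and RCT uptake is unknown.
- *That the class draw already supplies the eligible counts.* A draw needs a list of classes, and further RCT eligibility criteria await the pilot.

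**Conclusion.** The point holds in a limited form. As stated, reach is a completion proportion. It excludes eligible youth who decline or do not consent and, unless participants are all allocated youth, those who never start. The reach component of the implementation question therefore cannot reveal low uptake.

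The possible size depends on uptake, which the article does not give. Under the assumed figures a stated 90% is compatible with uptake anywhere from 20% to 80% in the RCT example and from 10% to 100% in the pilot example. These ranges show only that the measure is insensitive to uptake; they do not predict it.

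The severity is modest. The consequence falls on the implementation answer and on judging to whom the findings apply, not on the randomized comparison.

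**What to change.** In Outputs: Intervention Implementation:

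1. Rename the present measure completion, defined as completers divided by youth who start the program.
2. Define reach as youth who start divided by eligible youth in the drawn intervention classes. In the pilot, divide by youth invited, as far as program staff can supply the count.
3. Report both when answering the implementation questions.

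The cost is some record keeping: staff must note eligible or invited youth per class as well as starters and completers. For the RCT this can be set up in advance, since recruitment begins only after the pilot. Pilot participants have already been identified, so invitation counts there may have to be recovered from staff and may be incomplete. The reported reach will be lower than under the present definition whenever uptake is below completion.
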